#### Statistical analyses

As primary analysis, we will compare the difference in proportion of patients with progressed/worsened disease state (as defined according to WHO score) until day 28 in both treatment groups (2-sample chi squared test). The aim is to demonstrate preliminary superiority of FX06 in prevention of worsened disease state in comparison to placebo (with standard of care) treatment. For the group comparison, the 5% significance level is considered.

With regard to secondary endpoints, these will be described by summary statistics stratified by treatment group and available visits and the treatment difference until day 28; the 95% confidence interval will be given. For selected secondary endpoints, linear mixed models will be applied to investigate the impact of treatment, time, treatment-by-time, and other factors such as demographics.

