### Randomization

A randomization list will be generated by an authorized person through the sponsor. Central randomization will be performed in a 2:1 allocation to FX06 and placebo stratified by WHO group (moderate: score 4–5 and severe: score 6) and centre. As randomization procedure, stratified block randomization will be applied. The randomization will be performed centrally within the eCRF System Open Clinica. Independent pharmacists will dispense the allocated treatment according to the computer-generated randomization list.

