### Sample size considerations

Based on our literature research [24–26], we estimate the frequency of patients who do not worsen their disease status under placebo (+SoC) to be 70%, since we include only hospitalized COVID-19 patients and not any ambulatory COVID-19 patients with mild disease state. We expect that FX06 (+SoC) improves this rate by approximately 15%. Following Spinner et al. and ICU estimations at the KGU Frankfurt, we also expect 15% less patients with progressed/worsened disease status in the group treated with FX06 (+SoC) compared to placebo (+SoC).

Applying a *Z*-test for proportions with continuity correction with a significance level of 5%, *n* = 291 patients (194 FX06: 97 placebo; without drop-outs) are required to demonstrate a treatment difference in the proportion of patients with progressed/worsened disease until day 28 with a power of 80%. Considering 5% drop-out, 306 (204 FX06: 102 placebo) patients need to be recruited.

Sample size was calculated with G*Power version 3.1.9.6 using the *Z*-test for the difference between two independent proportions with continuity correction. Sample sizes were reconfirmed using PASS 16.0.2.

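### The primary chi-squared test ignores the WHO-group stratification; if WHO group predicts worsening, the test is conservative and gives up a little power, and its continuity correction is not stated

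*Protocol article*

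**What the plan says.** In the Randomization section of the article, allocation is 2:1 in stratified blocks, "stratified by WHO group (moderate: score 4–5 and severe: score 6) and centre". The Trial design section says the same.

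The Statistical analyses section fixes the primary comparison as the proportion of patients with worsened disease "until day 28 in both treatment groups (2-sample chi squared test", and adds: "For the group comparison, the 5% significance level is considered". It names neither stratification factor and does not say whether the test is continuity-corrected. The 95% confidence interval in that section belongs to the sentence on secondary endpoints.

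Centre appears once more, under Bias and limitations, where sensitivity analyses compare endpoints between centres descriptively or through regression effects. The article describes no analysis of the primary endpoint that uses WHO group.

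The Sample size considerations section rests on a Z-"test for the difference between two independent proportions with continuity correction", at the 5% level with 80% power. It gives 291 evaluable patients (194 FX06, 97 placebo), and 306 after allowing for drop-out.

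**The concern.** Stratified blocks force near-equal proportions of each WHO group in both arms. If the groups differ in risk, this balance removes the between-group part of the variance from the treatment difference. The pooled chi-squared statistic still counts that part. Its standard error is then too large, its real error rate falls below 5%, and some power is given up. WHO group is recorded at randomisation, so using it costs nothing.

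A second, smaller matter is that the sizing used a continuity correction and the primary analysis is silent on it. Near the 5% boundary that choice can decide the result, so it should not remain open until after unblinding.

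**Working it through.** **1. The plan's sample size.** Inputs from Sample size considerations: worsening 30% on placebo (70% not worsening) and 15% on FX06, ratio r = 2, 5% level, 80% power. Sidedness is not stated; two-sided reproduces the figure.

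Pooled rate = (0.30 + 2 × 0.15)/3 = 0.20.

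Uncorrected placebo n = [1.960 × √(1.5 × 0.20 × 0.80) + 0.8416 × √(0.30 × 0.70 + 0.15 × 0.85/2)]² / 0.15² = (0.9602 + 0.4403)² / 0.0225 = 87.2, rounded up to 88, total 264.

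Corrected n = (87.18/4) × [1 + √(1 + 2 × 3/(87.18 × 2 × 0.15))]² = 96.9, rounded up to 97, total 291. This matches the plan, so 291 is the corrected-test figure.

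**2. Correction or no correction.** The squared pooled Z statistic is the Pearson chi-square, and the squared corrected Z is the Yates chi-square. Full binomial enumeration at 194:97 gives:

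| Test | Power, 30% vs 15% | True size at a common rate of 30% |
|---|---|---|
| Corrected | 80.4% | 3.6% |
| Uncorrected | 84.3% | 5.1% |

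An example where the choice matters is 29/97 versus 38/194 worsened. The cross-product difference is 29 × 156 − 68 × 38 = 1940. The uncorrected statistic is 291 × 1940² / (97 × 194 × 67 × 224) = 3.88, p = 0.049. With the correction, 1940 becomes 1940 − 145.5 = 1794.5, the statistic is 3.32, and p = 0.069.

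**3. Size of the unstratified test.** The article gives no risks by WHO group, so the following are assumptions: 70% moderate, 30% severe, allocation balanced within strata, and overall placebo risk about 30%. Under no treatment effect, the pooled test uses P(1 − P), with P the overall risk, while the true variance is proportional to Σ w·p(1 − p) over the strata. The real critical value is therefore 1.96 × √[P(1 − P)/Σ w·p(1 − p)].

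| Placebo risk, moderate/severe | Σ w·p(1 − p) | P(1 − P) | Real critical value | True size |
|---|---|---|---|---|
| 30%/30% | 0.2100 | 0.2100 | 1.96 | 5.0% |
| 25%/42% | 0.2043 | 0.2104 | 1.99 | 4.7% |
| 20%/53% | 0.1867 | 0.2096 | 2.08 | 3.8% |
| 15%/65% | 0.1575 | 0.2100 | 2.26 | 2.4% |

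**4. Power, by simulation.** Unstratified chi-square against Cochran-Mantel-Haenszel (CMH) by WHO group, both uncorrected, 194:97. FX06 risks come from a common odds ratio that gives 15% overall.

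| Placebo risk, moderate/severe | Gap (points) | Size, unstratified vs CMH | Power, unstratified vs CMH |
|---|---|---|---|
| 30%/30% | 0 | about 5% for both | 84.3% vs 84.2% |
| 25%/42% | 17 | 4.8% vs 5.0% | 85.0% vs 85.4% |
| 20%/53% | 33 | 3.9% vs 5.0% | 85.1% vs 87.1% |
| 15%/65% | 50 | 2.4% vs 5.0% | 87.3% vs 91.4% |

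Simulated sizes agree with step 3 to within 0.1 point. A separate normal approximation, with 20% to 50% of patients severe, gives gains of 0.1–0.2, 0.5–0.7, 1.2–1.6 and 2.2–2.7 points for gaps of 10, 20, 30 and 40 points.

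**5. Adding individual centres.** A smaller simulation (20 centres and blocks of 6 assumed, 4,000 runs, Monte Carlo error about 0.3 to 0.6 points) compared CMH by WHO group × centre with the unstratified test. If neither factor is prognostic, power is 84.0% vs 85.9%, a loss. If both are strongly prognostic it is 87.7% vs 85.1%, a gain.

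**The case against.** The strongest reply is that little is at stake. Nothing in the article shows how strongly WHO group predicts this endpoint. Worsening is judged against each patient's own baseline score, so baseline severity need not predict it as it would an absolute outcome. For gaps of 10 to 20 points the gain is under one point of power, and the 50-point gap is an extreme assumption. The error is on the safe side, so a positive result would stand. The article also calls its methods section a short summary and points to additional files, where an adjusted analysis may exist. All of this stands, and it limits the point to a conditional one. It does not remove it, because the article does name the primary test, and that test leaves out a randomisation factor already in hand.

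Three stronger readings are tempting but unsupported:

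- A reader might infer that the trial was sized for a different test. The two-proportion Z-test and the chi-square are the same test; only the continuity correction is open, and power reaches 80% either way.
- A reader might infer that power is certainly wasted. That depends on prognostic strength, which the documents do not give.
- A reader might infer that the primary confidence interval will be too wide. The article fixes no interval method for the primary endpoint.

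**Conclusion.** The point holds as a conditional efficiency issue with a wording gap. Randomisation is stratified and the primary test is not. For assumed placebo gaps of 17 to 50 points between WHO groups, true size is about 4.8% to 2.4% and the power given up is about half a point to four points. With no gap the two tests are practically equal. These figures rest on the plan's 30% versus 15% at 194:97 and on assumed stratum risks and a 70:30 mix. Type I error is not inflated, and the sample size stands: the stated 80% describes the corrected test (exact 80.4%), while the uncorrected test has about 84%.

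**What to change.** - Make the primary test a CMH test stratified by WHO group (4–5 versus 6), without continuity correction, and report a Mantel-Haenszel risk difference with a 95% confidence interval.
- Keep the unstratified chi-square as a sensitivity analysis.
- Do not stratify the primary test by individual centre, because sparse strata can cost power. Address centre in a sensitivity analysis, pooled by a rule set in advance, for example by country.
- State that the 80% in the sample size section refers to the continuity-corrected test, and that the uncorrected test has about 84% at 291 evaluable patients.

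The cost is a change of wording in the protocol or analysis plan before unblinding. WHO group is already recorded, and neither the sample size nor the conduct of the trial changes.

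### Continuous secondary endpoints are compared both as values and as change from baseline, with no baseline-adjusted difference named; adjustment would sharpen the estimates at no cost (low severity)

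*Protocol article*

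**What the plan says.** In the protocol article, Secondary objectives and endpoints introduces its list as comparisons between FX06 and placebo at all available visits. For PaO2, FiO2, Horowitz index, oxygen saturation, breathing rate and the blood parameters, the list gives both the measured value and its change from baseline. It does not say which of the two carries the treatment comparison. The footnotes to Table 1 place blood sampling before the first dose, so baseline laboratory values are planned. Lung function is recorded only where it is measured routinely.

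Statistical analyses summarises the secondary endpoints by arm and visit and adds "the treatment difference until day 28; the 95% confidence interval will be given". No adjustment is mentioned for that difference. For selected secondary endpoints, "linear mixed models will be applied to investigate the impact of treatment, time, treatment-by-time, and other factors such as demographics". Demographics are named as an example of a further factor; the endpoint's own baseline value is not.

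Statistical methods describes the text as a short summary and refers to additional files for detail. Those files are not at hand.

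**The concern.** When an endpoint has a baseline measurement, there are three common ways to estimate the treatment difference: compare follow-up values, compare changes, or compare follow-up values adjusted for baseline. The article names the first two as comparisons and does not name the third.

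A difference in follow-up values carries part of any chance baseline imbalance forward. A difference in change usually over-corrects for it, because extreme baseline values tend to move back towards the mean. The two answers for one endpoint will therefore differ, and nothing in the article says which to read. Each also generally has a wider confidence interval than the collected data require.

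At stake is how clearly the trial can speak on oxygenation, breathing and inflammation, which matter for interpreting a phase II result alongside the primary endpoint.

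**Working it through.** **Arm sizes.** The only design figure in the article is the sample size for the primary endpoint. Its inputs, from Sample size considerations, are:
- a Z-test for "proportions with continuity correction with a significance level of 5"%, taken as two-sided, "with a power of 80"%;
- no worsening "under placebo (+SoC) to be 70"%, so 0.30 worsen on placebo;
- "We expect that FX06 (+SoC) improves this rate by approximately 15"%, read as percentage points, so 0.15 worsen on FX06;
- 2:1 allocation.

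The pooled rate is (0.30 + 2 × 0.15)/3 = 0.20. Before correction, placebo n = [1.960 × √(1.5 × 0.20 × 0.80) + 0.842 × √(0.30 × 0.70 + 0.15 × 0.85/2)]² / 0.15² ≈ 87.2. The continuity correction gives (87.2/4) × [1 + √(1 + 6/(2 × 87.2 × 0.15))]² ≈ 96.9, so 97 placebo and 291 in total. This matches "patients (194 FX06: 97 placebo; without drop-outs) are required". The recruited number is taken as stated: "Considering 5% drop-out, 306 (204 FX06: 102 placebo) patients need to be recruited". No SD, correlation or power is given for any continuous endpoint.

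**Gap between the two unadjusted estimates.** For one endpoint, the difference in values minus the difference in change equals the baseline difference between arms. In SD units, and ignoring stratification, its standard error is:
- 204:102: √(1/204 + 1/102) = 0.121, and 1.96 × 0.121 = 0.24;
- 194:97: √(1/194 + 1/97) = 0.124, and 1.96 × 0.124 = 0.24.

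Given an imbalance d, with equal SDs and baseline-to-follow-up correlation ρ, the difference in values is off by ρd and the difference in change by −(1 − ρ)d.

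**Precision.** With SD = 1 at both times, the variance factors are 1 for values, 2(1 − ρ) for change and 1 − ρ² for the baseline-adjusted difference. Relative to the adjusted variance these are 1/(1 − ρ²) and 2/(1 + ρ). The correlation is an assumption. Standard errors are in SD units at 194:97.

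| ρ | SE, value | SE, change | SE, adjusted | Variance ratio, value | Variance ratio, change |
|---|---|---|---|---|---|
| 0.3 | 0.124 | 0.147 | 0.119 | 1.10 | 1.54 |
| 0.5 | 0.124 | 0.124 | 0.108 | 1.33 | 1.33 |
| 0.7 | 0.124 | 0.096 | 0.089 | 1.96 | 1.18 |

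Taking square roots, confidence intervals are about 5%, 15% and 40% wider than adjusted ones for values, and about 24%, 15% and 8% wider for change. Over ρ = 0.2 to 0.8 the variance ratios run from 1.04 to 2.78 for values and from 1.67 to 1.11 for change.

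**Unequal SDs.** With baseline SD s₀ and follow-up SD s₁, the excess variance over the adjusted estimate is proportional to ρ²s₁² for values and (s₀ − ρs₁)² for change. Neither can be negative, so the ordering does not depend on equal SDs; only the size does.

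**Simulation.** With 10,000 runs for each of ρ = 0.3, 0.5 and 0.7, arms of 194:97 and a true effect of 0.3 SD, all three estimates averaged 0.30. The value and change differences had opposite signs in about 1% to 2% of runs. They fell on different sides of nominal 5% significance in about 30%.

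**The case against.** The strongest objection is that the point rests on silence in a condensed article. Detail is deferred to additional files, the mixed model covers only selected secondary endpoints, and its list of factors is open-ended. A reader might infer that the plan leaves the baseline value out of the model. The documents do not show that: nothing excludes it, and the article does not say whether baseline enters as a time point of the outcome. A missing covariate list alone would be no finding. What stands is narrower: both scales are listed as treatment comparisons, and the reported difference is described without adjustment.

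A reader might also infer that the two scales give conflicting answers. They do not in the sense of bias. Both estimate the same effect and differ only by chance imbalance, though their nominal significance can disagree.

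The gain can be restated as power. An effect with 80% power on the better unadjusted scale would have about 84%, 90% and 86% after adjustment at ρ = 0.3, 0.5 and 0.7. That is hypothetical, because the article states no power for these endpoints and names the 5% level only for the primary comparison.

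Two points reduce the size. Entry requires oxygen saturation of at most 92% on room air and at least 20 breaths per minute. This can truncate the baseline range, upset the equal-SD assumption and lower ρ, and with it the gain over comparing values. Randomization is also stratified by WHO severity group and centre, which limits imbalance in measures related to severity. Both shrink the gain without removing it.

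Finally, a reader might extend the point to plasma ADM. That marker is an explorative objective, and the sentences quoted here concern secondary endpoints only.

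**Conclusion.** The point holds as a low-severity, free improvement. For the continuous secondary endpoints measured at baseline, the article lists two unadjusted comparisons without choosing between them and does not name the more precise adjusted one.

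By chance alone the two differ within about ±0.24 SD (95% range) at 204:102, somewhat less where stratification helps. With equal SDs and ρ between 0.3 and 0.7, the variance exceeds the adjusted variance by 10% to 96% for values and by 54% down to 18% for change. These percentages rest on an assumed ρ.

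This is not an error in the primary analysis: the primary endpoint, sample size and error rate are unaffected. Nor is it shown that the final models ignore baseline, since the additional files may settle it.

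**What to change.** In Statistical analyses, add a sentence to this effect: for each continuous secondary endpoint measured at baseline, the treatment difference and its 95% confidence interval are adjusted for the baseline value of that endpoint. Either of two models will do:
- a mixed model on post-baseline values with treatment, visit, treatment-by-visit, the baseline value and baseline-by-visit;
- a longitudinal model with baseline as one of the outcome times and a common baseline mean in both arms.

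The second retains patients without a baseline value, which is useful for lung function because it is recorded only when routinely measured. Keep values and change from baseline as descriptive summaries by arm, and say so in Secondary objectives and endpoints.

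The cost is a sentence or two, settled before unblinding, and the extra model terms; no new data, visits or patients are needed. If the additional files already specify this, only the two sections of the article need to be aligned with them.

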## Discussion

### Bias and limitations

We expect a neglectable bias with regard to lack of compliance since all patients will be treated in hospital the entire time during the treatment period. Since we investigate the disease progression under FX06 treatment in several countries, a bias might arise when quality standard of care differs between countries. While this might impact the size of the primary endpoint, the assumptions on the treatment difference of the primary endpoint should not be impacted, since the randomization protects from imbalances within this regard within the different countries. Furthermore, as sensitivity analyses, endpoints will be compared descriptively among centres, or as effects of the regression models. Due to the double-blind study design, the risk of potential biases should be minimized.

Potential limitations might refer to a lack of recruiting and drop-out due to various possible protocol violations. While we controlled for drop-outs in the same size estimation, recruitment problems may be subject to external problems difficult to control for. One reason for the difficult recruitment are the competing ongoing trials on COVID-19, while at the same time a patient may not want to be assigned a placebo treatment although it represents standard of care.

### Discussion

The ongoing COVID-19 pandemic is affecting people worldwide since the first reported case. Up to the end of March 2022, more than 460 million cases and up to 6 million deaths have been reported [27].

With changing variants and the anti-vaccine movement, COVID-19 is still putting stress on ICUs. Therefore, we need new and diverse pharmaceutical options to treat COVID-19. FX06 might be a promising approach by targeting the inflamed endothelium of the host.

The IXION trial will answer the question whether FX06 has the potential to prevent progression from a moderate to severe/critical COVID-19 stage.

Furthermore, we like to identify specific molecular “Fingerprints” of the complex interaction between the endothelium and immune system. This might help to understand other conditions with endothelial dysfunction and capillary leak (e.g. sepsis and acute respiratory distress syndrome).

### Trial status

Study protocol (V1.1) was finalized at 12th of January 2022. This trial was registered with the responsible federal authority (Bundesinstitut für Arzneimittel und Medizinprodukte – No. 61-3910-4045190) and European Union Drug Regulating Authorities Clinical Trials Database (EudraCT no.: 2021-005059-35). Recruitment and enrolment of the patients will start at the end of 2022. The planned recruitment lasts 18 months.

## Data Availability

The datasets generated and/or analysed during the current study are available from the corresponding author on reasonable request after the end of the trial.

## Abbreviations

ACE2: Angiotensin-converting enzyme 2
AE: Adverse event
ALT: Alanine aminotransferase
ARDS: Acute respiratory distress syndrome
AST: Aspartate aminotransferase
bio-ADM: Bioactive Adrenomedullin
BL: Baseline
BMI: Body mass index
C: Concentration
CI: Confidence interval
Cl: Clearance
COPD: Chronic obstructive pulmonary disease
COVID-19: Coronavirus disease 2019
CRP: C-reactive protein
CRT: Capillary refill time
ct: Cycle threshold
DMP: Data Management Plan
e.g.: Exempli gratia; for example
ECMO: Extracorporeal membrane oxygenation
FiO2: Fraction of inspired oxygen
FU: Follow-up
GCP: Good Clinical Practice
GCSF: Granulocyte-colony stimulating factor
GGT: Gamma-glutamyl transferase
GMP: Good Medical Practice
HI: Horowitz index
i.v./IV: Intravenous
(S)AEs: (Serious) adverse event
ICAM-1: Intercellular adhesion molecule 1
EQ-5D-5L: Patient Reported Outcome (PRO)-Instrument
ICU: Intensive care unit
IgG: Immunoglobulin G
IIT: Investigator-initiated trial
IL: Interleukin
IMP: Investigational Medicinal Product
IUD: Intrauterine devices
MRI: Magnetic resonance imaging
SoC: Standard of care
SCR: Screening
STEMI: ST-segment elevation myocardial infarction
WHO: World Health Organization
